**Figure 1 BMJOPEN2016012253F1:**
[figure not shown]
Study flow chart.

### Data collection and recruitment

Data collection will be carried out using a Concerto clinical portal (V.8.3) and database (Orion Health, London, UK), embedded within the Trust's IT system. All AKI alerts (discussed below) are visible to the study team in a list in Concerto. Patients not previously enrolled in the study can be virtually ‘transferred’ into the study database at enrolment.

A key point is that each patient can only be recruited once to the study, and thus a given patient cannot be recruited to the before phase, and then later to the after phase. This avoids the ethical issue of double recruitment. Thus, a patient enrolled during the before phase cannot be enrolled in the after phase, if they have a further episode of AKI. The recruitment of more ‘recurrent’ patients with AKI during the 8-week before phase presents a potential limitation, but in our view, it is balanced by the much longer 20-week after phase.

Patients enrolled in the intervention (Heartlands after phase) group remain a ‘customer’ in the care of the AKI Outreach team if they have a recurrent episode of AKI, and their clinician(s) can receive further Outreach intervention(s) as required. In practice, we believe that this is the way any AKI Outreach team will work in future. The study recruitment will run from mid-2015 to later in 2016.

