### Statistical analysis

The focus of the study is to assess feasibility of all aspects prior to full-scale evaluation. The data collected in this pilot study will be used to assess the uncertainty of the primary outcome. Further analyses will separately compare the before and after arms at the intervention and control sites. We note that the intervention and control sites cannot be directly compared. The control site data will be used to assess any ‘system-wide’ change in AKI outcomes. Additionally, survival analyses will be carried out, examining time to first composite primary outcome, and Kaplan-Meier survival curves produced for each of the four groups. This pilot study is not powered to provide a full comparison of the before and after phases. Among the end points, the use of dialysis and frequency of non-dialytic AKI complications will give an indication of the safety of the intervention. We will analyse estimated Glomerular Filtration Rate (eGFR) and CKD stage at a group level and changes at individual patient level. We will also explore the potential of using these data to validate our previous prognostic index.^9^

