### Discussion and limitations of the study

The national algorithm for staging of AKI means that identification of patients with AKI is standardised. The ‘opt out’ consent process enables large-scale recruitment. The ethos of AKI Outreach is that advice is offered to the primary clinician, who may choose to act upon or ignore that advice. A key challenge in implementing the intervention is reaching and influencing the decision maker(s) within the primary team, especially as they have varying roles and beliefs.

The AKI Outreach service runs only 40 hours/week and not out-of-hours. As this is a pilot for a full CRT, there were only two sites and randomisation was not undertaken. Inevitably, the intervention and the control sites are different to a certain extent. The latter does not have on-site nephrology services. A full CRT is needed to provide a definitive answer regarding any benefits of this approach. What would a successful pilot look like? The delivery of recommendations acceptable to clinicians, comparable to our previous work (median of 3 within a median of 15 hours), and to large numbers of patients is a key indicator of success. The control group should show no evidence of a system-wide change in before and after AKI outcomes. The intervention group will provide evidence of the feasibility and safety of the intervention.

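### The longer after phase does not balance the excess of recurrent-AKI patients in the before phase: under once-only enrolment it lowers their share of the after cohort further

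*Protocol article*

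**What the plan says.** Under 'Data collection and recruitment', the article states that "each patient can only be recruited once to the study", and that "a patient enrolled during the before phase cannot be enrolled in the after phase, if they have a further episode of AKI". It recognises that this brings more recurrent patients into the before phase, and says this "presents a potential limitation, but in our view, it is balanced by the much longer 20-week after phase". No figure or mechanism is given for the balance.

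Two later statements depend on the two cohorts being comparable. Under 'Statistical analysis': "Further analyses will separately compare the before and after arms at the intervention and control sites". Under 'Discussion and limitations of the study', as a mark of a successful pilot: "The control group should show no evidence of a system-wide change in before and after AKI outcomes". The article also says that "This pilot study is not powered to provide a full comparison of the before and after phases".

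**The concern.** Patients who have AKI often are the most likely to alert early. With one enrolment per patient they are used up early, while patients with a first episode keep arriving. The before cohort is therefore relatively rich in recurrent patients and the after cohort relatively poor in them. Lengthening the after phase dilutes them further; it does not restore the before-phase mix.

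If recurrent patients differ in their risk of death, dialysis or stage progression, this shift in case mix alone moves the before/after contrast at both sites. At Heartlands it would mix with any Outreach effect. At Good Hope it could produce or hide the system-wide change whose absence counts as success. The control site does not remove the shift in the planned analyses, because the article says that the two sites cannot be directly compared.

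**Working it through.** **Plan's own figures ('After phase sample size').** Half-width = 1.96 × √(0.40 × 0.60 / n).
- n = 1000: 0.030, so 37.0% to 43.0%.
- n = 370: 0.050, so 35.0% to 45.0%.

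Both reproduce and are not in dispute. They are the yardstick for size below.

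**Inputs.** From the article: once-only enrolment, a before phase of 8 weeks (1.84 months) and an after phase of 20 weeks (4.60 months). Assumed, because the article gives no figures: the episode rate r of recurrent patients, their share of the before cohort, and their excess risk. In steps 1 and 3 first-episode patients are taken to arrive at a constant weekly rate.

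**Step 1: recurrent enrolment per week, after relative to before.** Captured before: c = 1 − exp(−1.84r). For an after phase of w weeks (m months), ratio = [(1 − c)(1 − exp(−r·m))/w] / [c/8].
- r = 1/3 per month: c = 0.46. At 20 weeks, (0.54 × 0.78/20)/(0.46/8) = 0.37.
- r = 1/6 per month: c = 0.26. At 20 weeks, (0.74 × 0.54/20)/(0.26/8) = 0.60 (from unrounded values).

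| Episode rate | 8-week after phase | 20 weeks | 40 weeks |
|---|---|---|---|
| 1 per 3 months | 0.54 | 0.37 | 0.23 |
| 1 per 6 months | 0.74 | 0.60 | 0.44 |

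A ratio of 1 would be balance. It moves away from 1 as the after phase lengthens.

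**Step 2: a second model with two patient classes.** First enrolments in weeks a to b are proportional to exp(−λa) − exp(−λb), where λ is a patient's weekly alert rate. Take recurrent patients as 5% of the population with one alert per 13 weeks, and 0.002 alerts per week for the others.
- Recurrent share before: 60%. After: 46%, 37% and 26% for 8, 20 and 40 weeks.
- Without the cross-phase bar, a 20-week window still has a share of 51% against 60% for 8 weeks, so the unequal lengths add imbalance of their own.
- Number enrolled after, per 1000 recurrent patients: 424 in 20 weeks against 248 in 8. The count rises while the share falls.

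This was repeated for one alert per 8, 13 or 26 weeks, with population turnover of 0, 2% or 5% per week, a 0- or 13-week gap between phases, and full or half capture of after-phase alerts. In every combination the recurrent share was lower after than before and fell as the after phase lengthened. The weakest effect of length was 60.3%, 60.1% and 60.0% for 8, 20 and 40 weeks, against 69% before.

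**Step 3: effect on the composite.** With before share p and ratio k, after share = pk/(pk + 1 − p). Shift = (p − after share) × excess risk.
- p = 20%, k = 0.37: after share 0.074/0.874 = 8.5%; the fall of 11.5 points × 0.10 to 0.15 = 1.2 to 1.7 points.
- p = 20%, k = 0.60: after share 0.12/0.92 = 13.0%; the shift is 0.7 to 1.0 points.
- Lowest case, p = 10%, k = 0.60, excess 10 points: 0.4 points.
- Highest case, p = 30%, k = 0.37, excess 15 points: 2.4 points.

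**Step 4: the part due to length alone.** At p = 20% and one episode per 3 months, an 8-week after phase has share 11.9% (k = 0.54) and a 20-week one 8.5%. The difference of 3.4 points × 0.10 to 0.15 = 0.3 to 0.5 points.

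**The case against.** The strongest reply is that the effect is small, disclosed, and confined to a further analysis in a feasibility pilot that is not powered for it. This largely stands. If before groups are proportional to phase length (1000 × 8/20 = 400 and 370 × 8/20 = 148), the before/after difference has a 95% half-width of about 5.7 points at Heartlands and 9.3 at Good Hope. A shift of 2.4 points or less would be hard to see there. But it is a bias, which larger numbers do not remove, and these estimates are meant to inform the cluster trial.

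A charitable reading of balance is that the longer phase recruits more recurrent patients in number and leaves a slightly smaller fraction of after-phase alert patients barred (24% against 28% for 8 weeks in the step 2 example). Both are true. Neither makes the two cohorts alike. Turnover is also real, since the background section gives AKI mortality above 23%, and it weakens the effect of length, as step 2 shows.

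A reader might infer more than the article supports:
- That recurrent patients disappear from the after phase. Only those already enrolled are barred; at one episode per 3 months, 54% remain eligible.
- That the plan compares the cohorts as if their case mix were equal. The article does not say that the comparison is unadjusted. It collects causes, comorbidities and medication, and adjustment may be set out in an analysis plan that is not shown.
- That the bias favours Outreach. Nothing in the article says that recurrent patients fare worse on this composite.

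**Conclusion.** The statement that the 20-week after phase balances the excess of recurrent patients is wrong under the article's own enrolment rule. The direction of the case-mix shift held in every scenario examined: a lower recurrent share after than before, and lower still with a longer after phase.

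The effect on outcomes is conditional. With recurrent patients making up 10% to 30% of the before cohort, one episode per 3 to 6 months, and a composite risk 10 to 15 points higher, the before/after contrast shifts by about 0.4 to 2.4 points in total, of which phase length is the smaller part. The shift is zero if risks are equal and reverses if recurrent patients fare better. It is below the planned half-widths of 3 and 5 points. The documents therefore do not support a claim that the pilot's conclusions would be overturned. They do support correcting the sentence and handling prior AKI in the within-site contrasts and the control-site criterion.

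**What to change.** 1. Delete the claim of balance. State instead that once-only enrolment gives the before cohort a higher share of recurrent AKI, and that the longer after phase does not correct this.
2. Flag prior AKI for every enrolled patient by running the alert algorithm on stored laboratory creatinines over the same look-back before each patient's alert in both phases. The look-back must be at least as long as the interval from the start of the before phase to the end of the after phase: 8 + 20 = 28 weeks plus any gap. Six months (about 26 weeks) is too short, because a patient enrolled early in the before phase could recur late in the after phase with a clean look-back and still be barred. Twelve months is an example. It should be checked against the actual dates, since recruitment is described as running from mid-2015 to later in 2016.
3. At each site, report the before/after contrast adjusted for or stratified by prior AKI, together with the contrast restricted to patients with no AKI in the look-back. In the restricted contrast the once-only rule has no effect, because anyone it bars already has an AKI episode in the look-back. Adjustment alone reduces the imbalance but may leave a difference in time since the last episode.

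The cost is one laboratory query, some analysis wording and slightly less precision in the restricted contrast. The recruitment rule and its ethical rationale are unchanged.

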### Core study methodology

To allow replication of the model throughout the wider NHS, we provide the updated TIDieR checklist (see online supplementary files).^24^

10.1136/bmjopen-2016-012253.supp2Supplementary file

#### Alerts

The electronic AKI alerts are the trigger for the afferent arm of the intervention. The alerts are generated within the laboratory software (Telepath, Computer Sciences Corporation) according to the national algorithm.^25^ It compares the current patient creatinine to a value in the past (baseline creatinine). The staging follows KDIGO guidelines for AKI,^26^ where 0 is no AKI and 3 is the most severe stage. Alerts are made visible to all users of the electronic patient records, with the stage being stated as part of all urea, creatinine and electrolyte reports. The alerts from our hospital laboratory also contain a hyperlink to online guidance, with separate guidance for hospital and community alerts. Alerts are not issued for patients in the dialysis units and renal wards. We refer to the current location of the patient when discussing community (primary care) or hospital alerts. Obviously some of the hospital alerts will represent what was community-acquired AKI, but Outreach focuses on the current location of the patient.

#### Hospital sites

The Heart of England Foundation Trust consists of three hospitals. Good Hope Hospital was selected as control site as it is larger and relatively similar to the intervention site of Heartlands Hospital in its services. For a detailed description of both hospitals, please refer to online supplementary file 1.

10.1136/bmjopen-2016-012253.supp1Supplementary file

#### Primary care sites

A large proportion of all AKI cases begin in the community. We, therefore, felt that it was important to include patients with AKI in the community in the study, as this provides the earliest opportunity to intervene in the care of the patient. Primary care clinicians see AKI alerts in the patients' electronic laboratory reports (implemented after consultation as part of the start of the study—about 9 months ahead of the national schedule). We have mapped >17 000 emergency admissions presenting to the three hospitals during a calendar month to identify which areas predominantly present to Heartlands hospital, and similarly to Good Hope hospital. We are, therefore, able to allocate any patient with AKI in the community in these postcodes to either the control (postcode areas B23, B24, B35, B43, B44 and B72–B79) or the intervention arms (postcode areas B7–B11, B25, B26, B33, B34, B36, B37, B40 and B46). A small number of general practices in our area do not use the hospital laboratories of the Trust, and therefore, any alerts for their patients were not available to the study team.

### After phase sample size

For the before phase, no sample size is required and eligible patients during the study period will be recruited. The sample size was calculated with the intent of estimating uncertainty of outcomes, to inform the design of the future cluster trial. Our previous work suggested that the combined outcome would be seen in about 40% of patients having an alert. With a sample size of >1000 (intervention group—Heartlands and area, after phase), a 95% CI of width 6% (37% to 43%) can be calculated. A sample size of 370 (control group—Good Hope and area, after phase) will allow us to produce a 95% CI of width 10% (35% to 45%).

### Study team

The AKI Outreach team will function during working hours, 5 days/week. The ideal service, addressing AKI 7 days a week, is beyond the resources of this pilot. The model is a mixed skills team, allocating tasks using an electronic list of alerts and the electronic study database. The core Outreach team consists of an experienced renal consultant (usually the Chief Investigator), renal research fellow (working at junior specialist registrar level) and a critical care research (trained in AKI care) nurse. The core clinical team members will be primarily responsible for delivering the interventions, in the form of telephone consultation, with or without a ward visit, triggered by the AKI alert. The core team members are supported by other research staff, who help with the research data collection. Each working day patients are prioritised according to AKI severity.

### Data collected

In the study database, we will collect data on the causes of AKI and the associated comorbidities for all patients, as well as medication used at the time of AKI. Causes will be determined in pragmatic fashion from the electronic records, including prerenal/renal hypoperfusion, nephrotoxic medications, intrinsic or specialist renal diseases (not covered elsewhere), urological/postrenal and surgical causes. We will determine comorbidities according to a modified Charlson scheme as previously reported,^9^ and in addition stage solid neoplasia using the Surveillance, Epidemiology, and End Results staging system.^27^
^28^

### Interventions

In majority of cases, interventions will be in the form of phone call to the clinical team looking after the patient. The phone call will be structured to obtain verbal consent of the clinician at the start of the call. The duration of the call will be tailored according to clinical complexity and expected outcome of the case. All interventions will be recorded on the trial database in order to measure ‘dose’. In view of the large numbers managed by a small Outreach team, we anticipate that most interventions will rely on a single call, with no follow-up. Key feasibility measures in the intervention phase will be the time from alert to intervention, and the median number of recommendations (in comparison to our previous work^17^).

### Intervention package

The Outreach team will advise on an evidence-based package of care (these interventions are limited to the intervention arm):
*Diagnostic and monitoring recommendations*—to rapidly establish a credible diagnosis of the cause of AKI including:
Improved assessment of volume status;Standardised use of urine dipstick (often missed);Appropriate sepsis investigations;Urgent ultrasound with suspected obstruction, while avoiding early ultrasound in patients at low risk of obstruction.*AKI treatment recommendations*—to treat correctable causes of AKI:
Rapid, limited treatment of hypovolaemia, with avoidance of iatrogenic fluid overload, recently recognised as a significant cause of mortality in AKI;Rapid sepsis therapy;Cessation of potentially nephrotoxic agents (many well known, such as ACE inhibitors and non-steroidal drugs, but others less well known such as Aciclovir);Urgent relief of urinary tract obstruction.*Recommendations to manage the acute illness:*
Where needed, recommendations will be made to address key aspects of the major underlying comorbidity;Improve nutrition, as malnutrition is known to be associated with poor outcome. Dietetic referral will be made for all appropriate inpatients with stage 3 AKI.*Pathway recommendations:*
For inpatients, refer to the Renal and/or Critical Care Outreach teams, as appropriate;For patients in the community, arrange urgent or immediate outpatient review or admission, as appropriate;Arrange formal palliative care when necessary.*Stage-based AKI management:*
Stage 1 patients will typically receive a single intervention call;Stage 2 patients will usually receive a single intervention call and be discussed with the renal consultant;Stage 3 inpatients will be reviewed by a consultant, ideally within 24 hours of the AKI Outreach team being aware of their presence in the intervention hospital (Heartlands Hospital);Rapid AKI follow-up clinic—we will offer surviving patients with stage 3 AKI a rapid follow-up clinic appointment, ideally within 7 days of discharge, or within 7 days of the alert if the patient is not admitted to hospital.

### The health economics substudy

We will pilot a prospective health economic assessment, calculating the cost of AKI. We aim to define with more accuracy the true total cost of an AKI episode. We will also pilot assessment of the costs of the Outreach service and its recommendations, using national tariffs for the latter. The information will be extracted from the electronic patient records or the paper records. The costs of long-term sequelae such as dialysis will be included. For the purpose of the pilot health economics substudy, we will obtain a sample of 50 patients, divided into 25 patients from the intervention group and 25 from the control group. We will open ‘recruitment weeks’ to run simultaneously at both sites until the numbers are met at each site. We will break down the service components (including, eg, the time of the phone call), any laboratory or radiological tests, and we will use the NHS cost codes. We will use the EQ-5D-5L questionnaire,^29^ which is a standardised short quality-of-life questionnaire, which has been used in various populations, including critically ill patients with AKI,^30^ since its development in 1990.^31^ We will record the five dimensions of health status and the visual analogue scale results,^32^ at the time of AKI (0 months). The EQ-5D-5L, and in addition a health resource use questionnaire (based on those from DIRUM (Database of Instruments for Resource Use Measurement)),^33^ will be completed by telephone at 3, 6, 9 and 12 months.

### Fidelity

We will pilot a fidelity assessment, examining intervention adherence, in conjunction with the health economic analysis, using the 25 patients recruited to the above analysis at the intervention site. In the fidelity and health economic work, each patient record will be examined in detail to extract the adherence to recommendations as well as all the costs of the admission.

### Quantitative analysis of clinical data

#### Estimates for the CRT

The main aim of this study is to test feasibility of the intervention and all study procedures. In addition, this pilot study will allow estimates of the uncertainty of the primary outcome (deterioration or death) to be used in planning a cluster trial. Secondarily, data from this study can be used to assess the prognostic model previously introduced. In addition, simple analyses will be conducted to look at CKD progression or development of end-stage renal disease as a result of AKI episode, and survival to discharge to a more dependent setting than at admission.

### Outcomes

The primary purpose of this study is to assess feasibility and inform a full cluster randomised study. The primary outcome for the full study, also collected in this study, is reflected in the trial acronym: deterioration or death of the patient with AKI, and is a combination of:
All-cause death within 30 days;Any need for dialysis or renal replacement therapy (intermittent haemodialysis (typically at the Renal Unit of Birmingham Heartlands Hospital) or continuous renal replacement therapy (typically in the intensive care units of the Trust)) within 30 days;Progression of AKI stage without dialysis within 30 days after the alert (stage progression is stage 1 deteriorating to 2 or 3; stage 2 deteriorating to stage 3).

These were chosen to reflect the major, potentially modifiable, outcomes of concern for patients (death and/or dialysis) and renal units or hospitals (death, dialysis or deterioration). Stage progression (compared to non-progression) is known to be associated with increased mortality and length of stay in a multivariate analysis,^34^ and is a useful surrogate end point.

Secondary outcomes for the main study, collected to assess feasibility here, are as follows:

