**Table d35e730:** 

Measured outcome	Time window
Percentage of patients admitted to hospital	Within 14 days of alert
Percentage requiring any critical care admission	During index admission
Other key events (see below)	During index admission
Percentage discharged to institutional care	After index admission
All-cause mortality	At 90, 182 and 365 days
Renal function (eGFR)	At 90, 182 and 365 days

In a pragmatic study, patients will not be recalled for renal function testing; at the time points above, we will use the last observation carried forward for all living patients. Key events are these events as given in the discharge letter:
Cause of AKI: new glomerulonephritis or new urinary obstruction diagnosis.Complication of AKI not requiring dialysis: new pulmonary oedema, uraemia ≥30 mmol/L or hyperkalaemia (≥6.0 mmol/L).

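### Stage progression in the composite is visible only on a repeat creatinine; Outreach may raise repeat testing in one of the four groups, so detection should be measured and death or dialysis reported alongside

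*Protocol article*

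**What the plan says.** The Outcomes section of the Protocol article defines a composite, intended as the primary outcome of the later cluster trial and also collected here. It combines death within 30 days, dialysis within 30 days, and "Progression of AKI stage without dialysis within 30 days after the alert". The last part is spelled out as "stage progression is stage 1 deteriorating to 2 or 3; stage 2 deteriorating to stage 3". Under Alerts, the laboratory software assigns the stage by comparing the present creatinine with an earlier one from the same patient.

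The Intervention package opens with "Diagnostic and monitoring recommendations". It also covers referral of inpatients to renal or critical care teams and urgent review or admission of community patients. The article states that "these interventions are limited to the intervention arm".

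Under Statistical analysis, before and after are compared separately at each site, and the control site is used to look for system-wide change. Survival analyses are added, "examining time to first composite primary outcome, and Kaplan-Meier survival curves produced for each of the four groups".

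**The concern.** Death does not depend on how often blood is tested, and dialysis largely does not. Stage progression does. A patient whose kidney function worsens and recovers without a second test leaves no record of it. No repeat creatinine is set for the 30-day window in any group, so detection follows whatever testing happens in routine care.

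The intervention can change that testing. Community patients are enrolled on purpose, and for them an alert without a prompt second test is plausible. Urgent review or admission is where a second test becomes likely. If testing rises in the Heartlands after group only, more progression is found there with no change in disease, and earlier tests also bring event times forward. The Good Hope before/after contrast would not show this, because Outreach is not delivered there.

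At stake are the reading of the Heartlands before/after contrast and the choice of endpoint for the cluster trial. Randomising clusters would not cure the problem, since Outreach would still be able to alter testing in one arm only.

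**Working it through.** **Step 1. The plan's own figures.** Under After phase sample size the article assumes a 40% composite. The half-width is h = 1.96 × √(0.40 × 0.60 / n).

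- n = 1000: h = 3.04 points, 37.0% to 43.0%.
- n = 370: h = 4.99 points, 35.0% to 45.0%.

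Both stated intervals reproduce. They describe sampling error in the composite as observed and say nothing about missed progression.

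**Step 2. Who can be affected.** Only patients at stage 1 or 2 at the alert can progress under the definition.

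**Step 3. Effect among stage 1 and 2 patients.** The article gives no progression rate and no retesting rate, so both are assumptions. Let π be the share who truly progress and t the share retested. Assume that retested patients are representative and that undetected progression is not counted. Detected progression is π × t, and the change is π × (t₁ − t₀). With π = 20%:

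| Retested before | Retested after | Change in detected progression |
|---|---|---|
| 80% | 90% | 0.20 × 0.10 = +2.0 points |
| 70% | 85% | 0.20 × 0.15 = +3.0 points |
| 60% | 80% | 0.20 × 0.20 = +4.0 points |

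Over all patients these must be multiplied by the share at stage 1 or 2 (below one, not given) and reduced for patients already counted through death or dialysis.

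**Step 4. Varying the assumed progression rate, starting from the 40% composite.** Let D be the share with death or dialysis (assumed 20% to 30%; the split is not given). Observed progression among the rest is 40% − D, so true progression is (40% − D) / t₀ and the new composite is D + (40% − D) × t₁ / t₀.

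| D | t₀ to t₁ | Implied true progression (all patients) | New composite | Shift |
|---|---|---|---|---|
| 30% | 80% to 90% | 12.5% | 41.3% | +1.3 |
| 20% | 60% to 70% | 33.3% | 43.3% | +3.3 |
| 30% | 70% to 90% | 14.3% | 42.9% | +2.9 |
| 20% | 70% to 90% | 28.6% | 45.7% | +5.7 |

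The upper rows are the extremes for a 10-point rise in retesting, the lower rows for a 20-point rise from 70%. The largest shifts exceed those in Step 3 because they imply true progression above 20%, and over all patients.

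A shift of this kind hides a true relative reduction in progression of 1 − t₀/t₁: 11% for 80% to 90%, 14% for 60% to 70%, and 22% for 70% to 90%.

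**Step 5. The right yardstick.** The bias falls on a before/after difference, so a one-group half-width of 3 points is not the comparison. Assume about 400 Heartlands patients in the before phase (1000 × 2/5, from phases of 2 and 5 months). The half-width of the difference is 1.96 × √(0.24/1000 + 0.24/400) = 5.7 points. Most of the shifts in Step 4 lie below that. Sampling error shrinks as a trial grows, but this shift does not, so it matters more in the cluster trial than here.

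**The case against.** The strongest reply is that extra testing is nowhere stated. The items listed under diagnostic and monitoring advice are volume status, urine dipstick, sepsis investigations and ultrasound; creatinine is not among them. Most interventions are expected to be a single call. The alert, with linked guidance, is visible to clinicians without any Outreach call. All of this stands. The rise in testing is an inference, best supported by the review and admission route for community patients, and it affects a subset of unknown size.

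Four stronger readings are tempting, and the article does not support them.

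- A reader might infer that patients with no second test are counted as not progressed. That is a natural default, but no such rule is printed, and an analysis plan that is not shown may set one.
- A reader might take the no-recall sentence as a rule for the 30-day window. It reads "In a pragmatic study, patients will not be recalled for renal function testing; at the time points above", and those points are 90, 182 and 365 days.
- A reader might count the stage 3 follow-up clinic as a source of extra detection. Patients at stage 3 at the alert cannot progress, and those who reach it later have already been counted.
- A reader might set a 3-point shift against the 3-point half-width. The shift in Step 3 concerns stage 1 and 2 patients, and the half-width concerns one whole group.

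It is also fair that the study is a feasibility pilot, not powered for the before/after comparison, and that its success criteria do not include a lower composite. Dialysis is already examined in its own right as a safety indicator. This lowers the stakes within the pilot. It does not remove them, because the pilot is meant to inform the use of this composite in the cluster trial.

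**Conclusion.** The concern holds as a risk of unequal detection, not as a demonstrated bias. Three facts are in the text: progression needs a later creatinine, no repeat test is set within 30 days, and a package confined to one group contains monitoring advice and a route to review or admission. If testing rises there, the direction follows: with disease unchanged, more tests can only raise detected progression.

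The size is unknown. With 20% true progression and retesting up by 10 to 20 points, detected progression rises by 2 to 4 points among stage 1 and 2 patients. The rise is smaller over all patients, and smaller still if sicker patients are already retested, since extra tests would then find fewer progressors. A true benefit could outweigh the effect, so an apparent worsening under Outreach is possible but not predicted. The remedy is cheap, and the pilot is the right place to measure the problem before the endpoint is carried forward.

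**What to change.** 1. Report death or dialysis within 30 days beside the composite in each before/after contrast and each Kaplan-Meier plot.
2. Tabulate, for each of the four groups and by hospital or community location at the alert, the percentage with at least one repeat creatinine within 30 days and the number of tests per patient.
3. Add a sensitivity analysis of the composite in patients who were inpatients at the alert, where testing can be expected to be closer to routine. Location at the alert is fixed before Outreach acts, so this restriction does not select on its effect.
4. Show progression with patients at stage 1 or 2 at the alert as its denominator.

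The cost is some extra tables from routine laboratory and study data, with no new patient contact. Death or dialysis has fewer events than the composite and is therefore estimated less precisely. The inpatient analysis is smaller and leaves out the community patients in whom the problem is most likely, so it supplements the testing table and does not replace it.
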